#### Implementation {16c}

Randomization procedures will be performed by an independent research professional not involved in other aspects of the trial.

### Assignment of interventions: blinding

#### Who will be blinded {17a}

Neither participants nor providers will be blinded in this study in the context of this pragmatic RCT. Even if the patient’s perception can be influenced by the type of provider they see, this approach is necessary because of the pragmatic nature of the proposed care model, and it is important that patients know which provider and models of care they are exposed to as this increases the external validity of the current trial. An independent statistician not involved in any other parts of this trial and blinded to the participants’ allocation will conduct the statistical analyses.

#### Procedure for unblinding if needed {17b}

Neither participants nor providers are blinded.

### Data collection and management

#### Plans for assessment and collection of outcomes {18a}

All data will be collected using the REDCap platform. Outcome measures will be collected at inclusion, before ED discharge, and at 4-week, 12-week, and 26-week follow points (Table 1).

#### Plans to promote participant retention and complete follow-up {18b}

In order to limit loss to follow-up, we will validate with participants at each time point their contact information and preferred means of communication.

#### Data management {19}

The databases will be centralized at the coordination center (Maisonneuve-Rosemont Hospital - MRH - Research Center). MRH will store all data captured in REDCap on its own servers. All data is therefore stored and hosted at MRH, and no project information is ever transmitted at any time by REDCap from MRH to any other institution.

#### Confidentiality {27}

Data will be kept in REDCap at the end of the study in a de-identified form using an identification code. Only the investigators will have access to the link key linking codes to individuals. The data will be kept for seven years.

#### Plans for collection, laboratory evaluation, and storage of biological specimens for genetic or molecular analysis in this trial/future use {33}

No biological specimens were collected.

## Statistical methods

### Statistical methods for primary and secondary outcomes {20a}

Descriptive statistics will be used to present the participants’ characteristics. Baseline demographic data will be compared across groups and the participating EDs to establish the comparability of study samples across intervention arms and clusters. If differences are observed, statistical models will be adjusted, and any difference will be considered. Descriptive statistics will be computed for all outcome measures at different measurement times. Per-protocol and intention-to-treat analysis will be performed. Outcomes will be analyzed at the individual level using mixed models as recommended for stepped-wedge designs [56]. A linear mixed model with a random effect for cluster and fixed effects for the intervention status and time period will be used for continuous outcomes including the primary outcome (BPI score). Separate analyses will be conducted on each of the secondary outcomes. In the case of non-normal outcomes, including re-visits and adverse events, a generalized linear mixed-model framework will be used. Time-driven activity-based costing (TDABC) will be the methodology used to capture the costs of providing services to achieve primary and secondary outcomes. TDABC’s micro-costing approach will allow us to precisely determine and differentiate the cost of providing care based on the specific types of patients. Measuring patient outcomes and costs to achieve those outcomes will provide a more rigorous approach to understanding the value of introducing innovative modifications to existing clinical pathways. This approach has the potential to compare costs, outcomes, and clinical pathways within single health care institutions, among regional care centers and across provinces.

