### Trial design {8}

This project is a multicenter pragmatic stepped-wedge (3 steps with 4 periods of 6 weeks each) cluster RCT with a cost analysis conducted in six Canadian EDs.

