**Interventions**						
**Usual ED physician care**						
**PT-led APP care**						
**Assessments**						
**BPI**	**X**			**X**	**X**	**X**
**Disability questionnaires (NDI, ODI, LEFS, quickDASH)**	**X**			**X**	**X**	**X**
**EQ-5D-5L**	**X**			**X**	**X**	**X**
**PHQ-9**	**X**					
**Numerical Pain Scale**			**X**			
**Standardized evaluation form (PT/MD)**			**X**			
**VSQ-9**			**X**			
**Health care resources utilization and health care costs:** **Treatment diary** **Patients’ medical file**				**X**	**X**	**X**

*ED* emergency department, *APP* advanced practice physiotherapy, *BPI* Brief Pain Inventory, *NDI* Neck Disability Index, *ODI* Oswestry Disability Index, *LEFS* Lower Extremity Functional Scale, *DASH* Disabilities of the Arm, Shoulder and Hand, *PHQ-9* Patient Health Questionnaire-9, *VSQ-9* Visit-Specific Questionnaire-9

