### Sample size {14}

The main hypothesis is that APP-led care will be at least as effective as usual ED physician care based on the results of our literature review [16] and ED studies [43, 44]. The sample size required is based on a target effect size of 0.35, using the primary outcome measure, the BPI short form, with a two-sided significance level of 0.05 and a power of 0.80. An intra-cluster correlation coefficient of 0.004 was assumed based on a prior cluster RCT that also used the BPI short form as a primary outcome [55]. The calculation further assumed 6 clusters with an exchangeable correlation structure within clusters, a total of 3 sequences (steps), and two clusters changing treatment per sequence. With these assumptions, the trial will be adequately powered if 27 individuals are accrued per cluster per sequence. Hence, we will recruit 31 patients per site per sequence, accounting for a potential loss to follow-up of 15%. The total sample of 744 participants (124 per site) will provide an adequate sample size to meet our objectives.

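### The primary model leaves out the baseline BPI that the trial collects, and the only covariate rule is an undefined one triggered by observed demographic differences

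*Protocol article*

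**What the plan says.** Section {20a} of the Protocol article names the model for continuous outcomes, including the BPI score: "A linear mixed model with a random effect for cluster and fixed effects for the intervention status and time period". Just before this, it says that baseline demographic data will be compared across groups and across the participating EDs, and continues: "If differences are observed, statistical models will be adjusted, and any difference will be considered". It does not say which variables count, what size of difference matters, or whether a test is used.

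Table 1 schedules the BPI at enrolment and at 4, 12 and 26 weeks. The row "Disability questionnaires (NDI, ODI, LEFS, quickDASH") and the EQ-5D-5L row follow the same schedule. The primary endpoint is BPI pain interference at 4 weeks (Primary outcome measure). Nowhere does the article use a baseline score as a covariate.

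**The concern.** There are two linked problems.

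- **An available covariate is not used.** The baseline value of the primary outcome is normally among the strongest predictors of its follow-up value. It is collected here at no extra cost, yet the named model does not contain it.
- **The stated route to adjustment is a poor one.** It depends on what the baseline table shows, so the covariate set is open until the data have been seen. It refers to demographic data, so an imbalance in baseline pain interference might trigger nothing.

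At stake are precision on the primary endpoint, protection against a chance or recruitment-related imbalance in baseline pain interference, and a primary model that is fixed in advance.

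**Working it through.** **1. Reproduce the plan's figure.** The inputs come from Sample size {14} and Trial design {8}:
- "The sample size required is based on a target effect size of 0.35" (standardised);
- "with a two-sided significance level of 0.05 and a power of 0.80";
- "An intra-cluster correlation coefficient of 0.004 was assumed";
- "6 clusters with an exchangeable correlation structure within clusters, a total of 3 sequences (steps), and two clusters changing treatment per sequence";
- "3 steps with 4 periods of 6 weeks each".

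The 27 analysable patients are read as per site per period, because 31 recruited × 4 periods = 124 per site, and 124 × 6 = 744, the stated total.

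The Hussey–Hughes variance, with total variance 1, is

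Var = I·s²(s² + Tτ²) / [(IU − W)s² + (U² + ITU − TW − IV)τ²].

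- I = 6, T = 4, τ² = 0.004, s² = 0.996/27 = 0.03689.
- U, the number of intervention cells, is 2 × (3 + 2 + 1) = 12.
- W, the sum of squared period totals, is 0 + 4 + 16 + 36 = 56.
- V, the sum of squared cluster totals, is 2 × (9 + 4 + 1) = 28.
- IU − W = 72 − 56 = 16.
- U² + ITU − TW − IV = 144 + 288 − 224 − 168 = 40.

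Var = 6 × 0.03689 × (0.03689 + 0.016) / (16 × 0.03689 + 40 × 0.004) = 0.01560, so SE = 0.1249. Power = Φ(0.35/0.1249 − 1.96) = Φ(0.842) = 80.0%. The plan's figure reproduces, and it takes no credit for a baseline covariate.

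**2. Add baseline BPI.** With r the correlation of baseline with 4-week BPI, multiply s² by (1 − r²), leave τ² unchanged, and keep 27 per cell. The article does not give r, so a range is assumed.

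| r (assumed) | Residual variance removed | SE | Power | Effect detectable at 80% power (SD) |
|---|---|---|---|---|
| none | 0% | 0.1249 | 80.0% | 0.350 |
| 0.1 | 1% | 0.1243 | 80.4% | 0.348 |
| 0.2 | 4% | 0.1226 | 81.4% | 0.344 |
| 0.3 | 9% | 0.1197 | 83.3% | 0.335 |
| 0.4 | 16% | 0.1154 | 85.8% | 0.323 |
| 0.5 | 25% | 0.1097 | 89.1% | 0.307 |

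**3. Would the stated rule bring in baseline BPI?** Baseline data collection (under Outcomes {12}) lists socio-demographic characteristics such as age, sex and income separately from clinical variables. Section {20a} compares demographic data. On an ordinary reading, baseline BPI is outside the trigger.

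**4. Is the trigger informative?** Sequence generation {16a} starts all six sites in control and ends with all six in intervention. By period, the control cells number 6, 4, 2, 0 and the intervention cells 0, 2, 4, 6. The average period is (6×1 + 4×2 + 2×3)/12 = 1.67 for control and (2×2 + 4×3 + 6×4)/12 = 3.33 for intervention. A crude arm comparison therefore mixes any calendar drift in case mix with arm differences. Differences between EDs in three provinces are to be expected, and the cluster effect already addresses them. Sites are told their sequence at the outset (Concealment mechanism {16b}), and site staff screen and consent individual patients (Recruitment {15}, {26a}). Randomising clusters therefore does not by itself protect comparability at patient level, which is a reason to fix the adjustment in advance.

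**The case against.** **The article may simply be condensed.** The named terms are structural, the list is not said to be exhaustive, and a full covariate list commonly sits in an SAP that is not shown. This stands in part: nothing in the article rules out baseline BPI, and its absence alone would not be a finding. But the article goes further than silence. It states a data-dependent rule, and an SAP that fixed covariates beforehand would have to replace that rule.

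**The power target is met without adjustment.** This stands. A reader might infer that the trial is underpowered because baseline BPI is missing; step 1 shows otherwise. The gain also rests on an assumed r and is under half a percentage point at r = 0.1.

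**The error rate is not shown to suffer.** A reader might also infer that looking first and adjusting afterwards inflates type I error. That is not supported. A null simulation of this layout used 27 per cell, fixed cluster and period effects, no cluster variance and six independent covariates, each adjusted for only if its arm difference was significant at 0.05. It gave 5.1% with a weak strongest covariate and 4.5% with a strong one, over 6,000 runs each. The Monte Carlo standard error is √(0.05 × 0.95/6000) = 0.28 points, so both are compatible with 5%. The simulation tests a mechanical rule, not analyst discretion.

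**An independent, blinded statistician does the analysis ({17a}).** This limits discretion but does not remove it. The model needs site and period; every first-period patient is control and every last-period patient is intervention, so blinding is hard to keep. Nor does blinding supply the missing variable list.

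**Recruitment has its own safeguards.** Triage lists are screened so that none are omitted, and participants are compared with non-participants ({15}). These help, and baseline adjustment would not remove selection on unmeasured factors. Neither point argues against prespecifying it.

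**Conclusion.** The point holds as a worthwhile improvement to a rule the article states, not as an error in its sample size or a demonstrated bias. The primary model as named omits a baseline measure of the primary outcome that the trial collects. The only covariate rule is undefined, depends on the data, and would not clearly reach that measure.

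The size is forgone precision: from about 0.4 percentage points of power at r = 0.1 to about 9 points at r = 0.5, on top of a stated 80% that stands. These figures assume the plan's effect size and ICC, 27 analysed per site per period, a normal test, and a baseline covariate that reduces only within-cluster variance. The direction of the gain is secure for any appreciable correlation; its amount is not known from the document.

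**What to change.** In section {20a}:

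- Add baseline BPI interference as a prespecified fixed covariate in the primary model.
- For the disability and EQ-5D-5L outcomes, add the baseline value of the same instrument.
- Remove the rule that adjusts when differences are observed, or confine it to a sensitivity analysis labelled as such.
- Keep the baseline tables descriptive, so that they trigger no change of model.
- Further covariates are optional; if any are wanted, list them before the data are seen.

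The cost is a sentence or two in the protocol and SAP. No new data are needed, and the sample size can stay as it is.

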### Interim analyses {21b}

Interim analyses will be conducted at the 1-month follow-up to ensure no safety issue is detected and final analyses will be conducted at the end of the trial.

### Methods for additional analyses (e.g., subgroup analyses) {20b}

Secondary analyses will be performed according to the affected body area (upper limb, lower limb, neck, or back) and will consider site recruitment clustering, since these factors can impact care utilization as well as other outcomes measured in the study. The same is also true for sex and gender for which secondary analyses will also be conducted.

### Methods in analysis to handle protocol non-adherence and any statistical methods to handle missing data {20c}

Participants withdrawing from the study and reasons for withdrawal will be analyzed. Characteristics of participants and non-participants will also be compared. Multiple imputation will be used for missing data handling.

### Plans to give access to the full protocol, participant-level data, and statistical code {31c}

The protocol, data, and statistical code that support the findings of this study will be available from the corresponding author, upon reasonable request.

### Oversight and monitoring

#### Composition of the coordinating center and trial steering committee {5d}

The trial steering committee (TSC) will include co-PIs Drs. [name], [name], and [name], with co-Is and assistants hired in each site. They will be at the core of trial management (as described above). The TSC will meet at the beginning of the study to plan/organize, to ensure the study integrates well within each site’s local reality. Twice a year, the TSC will meet to produce an executive summary of the research program. The research team from Maisonneuve-Rosemont Research Center, under [name] supervision, will coordinate the study.

#### Composition of the data monitoring committee, its role, and reporting structure {21a}

Since this is a low-risk intervention and not required by the Ethics Committee, there is no external data monitoring committee.

#### Adverse event reporting and harms {22}

The current literature on the safety of ED physiotherapy care with MSKD patients found no increase in adverse events associated with ED physiotherapist-led care [16, 43]. Moreover, physiotherapists will systematically present to an independent ED physician requests for medical imaging and diagnostic tests, medication prescription, or referrals to other providers, to respect medical legislation and ensure safety. Any adverse events will be documented and fully detailed. They will also be communicated to the CIUSSS-de-l’Est-del’Ile-de-Montréal Ethics Committee and reviewed by the co-principal investigators and co-investigators.

#### Frequency and plans for auditing trial conduct {23}

The TSC will meet every month to discuss issues with recruitment, protocol adherence, and follow-up of participants.

#### Plans for communicating important protocol amendments to relevant parties (e.g., trial participants, ethical committees) {25}

If any important protocol amendments are required, the TSC will meet to discuss the relevance of the proposed changes. Ethics committees of all participating sites will be informed of potential changes. Amendments will be undertaken only after approval of all committees.

#### Dissemination plans {31a}

Several stakeholders and knowledge users, such as patients, administrators, health care practitioners, and decision-makers, have been engaged in the entire process from project inception to preparation of this protocol. They will pursue their active involvement until project completion and dissemination of the results. The results of this study will be adapted for presentation and exchange with collaborators in the different trial settings. A set of recommendations based on the results will be developed and shared. The results of this study, with the involvement of our collaborators and knowledge users, will be presented in each participating hospital through formal on-site or distance meetings and symposiums. Other usual means of dissemination will include communications in conferences related to ED and trauma research and practice (e.g., emergency medicine), rehabilitation or health service organization, and scientific publications in peer-reviewed journals. Outcomes will also be shared with stakeholders (medical and patients’ associations and governments) by producing and sharing policy briefs and synthesis documents.

## Discussion

Current evidence shows that an increasing number of MSKD patients turn to EDs for care [57]. Many studies have shown that the current management of MSKD is often not optimal and is associated with poor outcomes [2, 15, 58]. Current training of ED physicians covers the management of serious, complex, and potentially life-threatening disorders. Training for other non-life-threatening disorders such as MSKD is often more limited. Also, current medical management of MSKD is often associated with high rates of opioid prescriptions [58, 59]. Indeed, Canada is struggling with an opioid crisis and many patients presenting to the ED for painful MSKD are discharged with an opioid prescription [60]. Even though opioids should not be the first-line treatment for the management of MSKD [58, 61–63], they represent a significant part of the current medical management of MSKD pain in the ED. Conversely, recommended non-pharmacological approaches [64], such as physiotherapy, are scarcely used. Studies involving PTs as primary care providers for patients presenting with MSKD have shown that early access to care leads to better outcomes as PTs are able to take more time with patients and can provide more complete education to patients and offer self-management strategies [65, 66]. Patients’ satisfaction with MSKD care is often significantly higher with PT led-care compared to physician care [66]. Our team recently completed two studies that serve as a foundation to the current trial. We first assessed the diagnostic concordance as well as management of ED patients with MSKD by ED PTs in comparison with usual ED physician care in two EDs [43]. The results showed that there was a high diagnostic agreement between PTs and ED physicians with no serious or non-MSKD pathologies being missed by PTs and no adverse event recorded. ED PTs were shown to recommend more physiotherapy care for MSKD, in comparison with usual ED medical care. ED physicians prescribed significantly more prescription drugs, including opioids, to manage MSKD in comparison with ED PTs. [43] The second study by our team was a single-blind pilot feasibility RCT conducted in another ED [44]. Although based on per-protocol analysis, patients that received ED PT-led care had significantly lower pain interference and pain intensity levels at 1 and 3 months after the initial ED visit. Lower proportions of prescription medication, including opioids and lower rates of re-visits to the ED, were also observed in comparison with patients receiving usual medical care at 1 month. ED PT-led care was also associated with significantly fewer prescriptions of medical imaging tests [44].

### Strength and limitations

This study is the first multicenter pragmatic trial with a cost analysis assessing APP-led ED care. The trial has been designed by a group of experts with expertise in the management of MSKD, public health, epidemiology, cost analyses, health services, ED medicine, interprofessional collaboration, rehabilitation, and designing and performing RCTs. The stepped-wedge design is an emerging and original methodology that facilitates the evaluation and implementation of new models of care [67].

Although this trial is a pragmatic design, because of its experimental nature, it may not fully represent usual care that APPTs or ED physicians offer as they are aware of the objective of the trial. Moreover, patients are not blinded to providers that will offer care, and it may influence their perceptions. Still, this approach is necessary because of the pragmatic nature of the proposed trial, and it is important that patients know which provider and models of care they are exposed to as this increases the external validity of the current trial. Also, only a limited number of APPTs (12) will be assessing patients within this study across six EDs across Canada.

While APP-led ED models of care are emerging globally, none of these models has been evaluated across Canada where these models are also becoming more prominent. MSKD not only represent a significant economic burden for Canadians, but also have a significant impact on population health, the Canadian workforce, and our health care system. As such, new models of care that result in more efficient care are needed. Given the high consultation rates for MSKD and known overcrowding in EDs, this trial has the potential to improve access and efficiency of ED care.

### Trial status

Recruitment for this trial should start in the fall of 2022 and be completed by the spring of 2023.

## Data Availability

After all analyses have been conducted and results published, the data that support the findings of this trial will be available upon reasonable request.

## Abbreviations

APP: Advanced practice physiotherapy
APPT: Advanced practice physiotherapist
BPI: Brief Pain Inventory
DASH: Disabilities of the Arm, Shoulder and Hand
ED: Emergency department
KT: Knowledge transfer
KU: Knowledge user
LEFS: Lower Extremity Functional Scale
MSKD: Musculoskeletal disorders
NDI: Neck Disability Index
ODI: Oswestry Disability Index
PHQ-9: Patient Health Questionnaire-9
PT: Physiotherapist
RCT: Randomized controlled trial
TSC: Trial steering committee
VSQ-9: Visit-Specific Questionnaire-9
